#### **4.3.4 The intervention package of care contains:**

- **Integrated NCD-COVID guidelines** to support RHC staff to deliver COVID care by triaging symptomatic patients; promoting rational use of personal protection equipment (PPE); promoting COVID vaccination; replacing face-to-face follow-ups by virtual consultation; and providing case management, health education, and home quarantine support. We will adapt our LMICs COVID-19 guideline into Pakistan to be embedded in the NCD (diabetes/ hypertension) care in the WDF project.
- **A telemedicine platform** containing a smart phone app component, to link patients with facility staff and community peers (champions). The technology will offer patients: a) access to knowledge on NCD and COVID care, including healthy lifestyle and behaviours to prevent COVID transmission; b) report care challenges being faced at respective RHCs (or at the referred facility); c) get peer-support (through technology assisted audio tele-conference of patient groups) for practicing recommended behaviours at home/ communities; d) get routine NCD follow-up advice; also seek advice on medical complaint/ condition. We will also explore the feasibility of using auto-generated messages through the digital application.
- **An ECHO based online platform** for staff training, mentoring and performance monitoring will be employed for case-based learning using best practice and data. RHC staff will be trained in screening, prevention and integrated management of Covid-19 and NCD, as well as how to use the mobile app and send health promotional SMS messages. Based on our experience in the Philippines and Sri Lanka, we will provide training to RHC staff and community health workers regarding how to improve vaccine confidence among high-risk groups for COVID-19, including NCD patients.

**Patients will receive:** 1) the option of attending virtual consultation with health providers in RHCs through smart phones, SMS or calls; 2) targeted health education for NCD and COVID; 3) hypertension and diabetes follow-up care through the telemedicine platform; and 4) COVID care and support through telemedicine. Patients who do not have access to smart phones will be helped by family members. We will also identify "patient champions" who are persons with lived experience of well managed diabetes, hypertension or COVID in the catchment area and are willing to provide consultation support to patients in the same area through the telemedicine platform. Creation of study materials and intervention components will be grounded in a gender and culturally responsive approach, informed by local stakeholders and best practices, to support equitable delivery of services and workforce capacity building.

**4.3.5 Outcome evaluation:** We will assess effectiveness through the following indicators measured at 10 months. Our **primary outcome** is the average systolic blood pressure (mmHg) measured in the RHC once a month of the last three months. Our secondary outcomes include: 1) the average diastolic blood pressure (mmHg) measured in the RHC once a month of the last three months; 2) percentage of patients with controlled BP measured below 140/90 mmHg for patients with hypertension but without diabetes, and

below 130/80 mmHg for patients with diabetes. The denominator will be all NCD participants in RHCs. The numerator will be patients with controlled BP, measured at 10 months; 3) random blood glucose (mmol/L); 4) body mass index (BMI); 5) attendance rate to monthly meetings with RHC doctors (face-to-face or digital); We will also measure indicators related with COVID-19: 6) proportion of patients who have had at least two COVID vaccinations; 7) proportion of patients reporting COVID symptoms; 8) proportion of patients who received COVID care (diagnosis, treatment or home support) from RHCs among those reported COVID-19 symptoms; and 9) proportion of participants been admitted in hospitals for any reasons; 10) mortality rate of participants for any reasons during the 10 months of follow up. We will collect blood pressures, blood profile, and patient body weight and height at Month 1 and 10 in the RHCs. Participants will be asked for fasting for 24 hours and provide a blood sample. During the consultation, the RHC doctor will measure the participants' BP using a calibrated electronic sphygmomanometer after 5 minutes of seated rest, and measure body weight and height. Blood samples will be collected and analyzed in RHC according to national guidelines for fasting plasma glucose. We will collect attendance rates using the routine patient treatment cards in RHCs to record both physical and virtual consultations. We will conduct a survey at the recruitment to collect patient demographics, socioeconomics, smoking status, any COVID symptoms of themselves or family members, health service use, and quality of life. The survey will be repeated at Month 10 in the last follow-up to collect COVID-19 vaccination, symptoms and related care utilization.

**4.3.6 Sample size and justification:** Sample size is based on demonstrating the intervention achieves a non-inferior result in systolic blood pressure (SBP). We will define a non-inferiority margin of 2.5 mmHg. The reasoning behind this is that SBP can be quite variable over the day, easily ranging 5 mmHg. Thus, if the intervention results in SBP no worse than control by 2.5 mmHg, it would represent non-inferiority. Based on prior work, the standard deviation of SBP is expected to be about 11 mmHg. For an individually randomized trial, a sample size of 332 per group would have 90% power with a one-sided type one error of 5% to demonstrate non-inferiority at a 2.5 mmHg margin. We will aim to recruit 40 patients per cluster. If we assume a modest intra-class correlation (ICC) of 0.03, indicating a sample size of 614 per group to achieve the same power. Thus, 15 clusters per group of 40 patients each will be required to obtain the minimal required sample size. Considering a 20% loss-to-follow-up rate based on our trials in Pakistani and China, we aim to increase to 50 patients per cluster, that is a total of 1500 patients to be recruited. Power will increase if all clusters meet the enrollment target of 50 patients; furthermore, the impact of averaging each patient's systolic blood pressure over the last 3 months should reduce the standard deviation, further increasing power. The reason for averaging is that single systolic blood pressure measurements are less representative of blood pressure.

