#### **4.6 Data collection, management, and analysis**

We will collect patients' demographic and social information, their exact home address, blood pressures, body weight, and height, knowledge, attitude and practice (KAP) regarding NCD and COVID at the randomization and Month 10 in the RHCs. The RHC doctor will measure the participants' blood pressure using a calibrated electronic blood pressure apparatus after 5 minutes of seated rest, and measure body weight and height. Participants will be asked to provide a blood sample in the RHC at the recruitment and Month 10. In addition, we will also collect patient blood pressures in Month 10 using same methods. Blood samples will be collected and analyzed in RHC according to national guidelines for fasting blood glucose. We will collect attendance rates using the routine patient treatment cards in RHCs to record both physical and virtual consultations. We will conduct a survey at the recruitment to collect patient demographics, socioeconomics, smoking status, COVID-19 immunization status, health service use, medial, KAPs for NCD and COVID, and health care and related costs. The survey will be repeated at Month 10 in the last follow-up to collection information regarding COVID-19 symptoms and related health care consultation and use. Any deaths that occur in patient group during this period will be assigned a probable cause, as determined by a method called verbal autopsy.

Overall, we will conduct mixed methods evaluation to examine the utility of the NCD-COVID guideline, the platforms and care process to inform acceptability, feasibility, reach, adoption, and implementation related challenges (in Section 5.2).

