**5. Project management:** The investigators will seek ethical approvals from the Research Governance Committees in Canada and Pakistan (if needed). The study will be conducted to protect human rights and dignity of the participants. The study has been designed to minimize the burden of participants and any foreseeable risks in relation with the interventions. Interventions of our care program have no known harms. Starting from the usual care period, all participant patients will receive study information in Urdu and English and be invited to participate in the study by research staff in RHCs. We will collect written consents where feasible. We will collect informed consents from all participants. [name] and [name] will be co-guarantees who have full access to the trial dataset. A trial management unit (TMU) will be established in Islamabad, Pakistan with a trial manager and one staff locally and a research coordinator from UofT. TMU will manage the day-to-day activities of the trial. [name] will be the lead statistician, supported by [name]. External member led DSMC will be established to safeguard the safety and privacy of patients involved, and to ensure that all data are collected according to agreed ethical guidelines, properly stored and only used for research purposes. A trial steering committee (TSC) will be established and led by external members. We will organise teleconference meetings for both the DSMC and TSC at the beginning of the study, and then on quarterly basis. The committees may also meet on an ad hoc basis should the need arise.

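### Secondary outcome 3 is named random blood glucose, but the only sample described is a fasting one, taken after an unexplained 24-hour fast with no exception for people with diabetes

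*Protocol*

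**What the plan says.** Section 4.3.5 lists ten secondary outcomes, the third of which is "random blood glucose (mmol/L". Later in that section the procedure reads: "Participants will be asked for fasting for 24 hours and provide a blood sample". It continues: "Blood samples will be collected and analyzed in RHC according to national guidelines for fasting plasma glucose".

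Section 4.6 covers the same ground. It gives the timing, "Participants will be asked to provide a blood sample in the RHC at the recruitment and Month 10", and then the assay: "Blood samples will be collected and analyzed in RHC according to national guidelines for fasting blood glucose". It states no length of fast.

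People with diabetes are among the participants. The blood pressure control outcome in section 4.3.5 gives them their own target, "below 130/80 mmHg for patients with diabetes". Section 4.3.7 recruits from patients registered with hypertension or diabetes, and the criteria in section 4.3.2 do not exclude diabetes.

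On burden, section 5 says: "The study has been designed to minimize the burden of participants and any foreseeable risks in relation with the interventions".

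**The concern.** Random and fasting glucose are different measurements. A random value is taken without regard to meals; a fasting value is taken after a set period without food. They are not interchangeable as outcome definitions. Section 4.6 has all continuous secondary outcomes modelled in a similar way to systolic pressure, so glucose gets its own between-arm comparison, and the protocol must settle which quantity is being compared. As it stands, sites could differ in what they collect, or the outcome could be renamed once data exist.

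The second issue is participant safety and burden. An instruction to fast for 24 hours, given to participants generally, reaches people with diabetes. The protocol offers no reason for that length and makes no allowance for anyone on glucose-lowering treatment.

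**Working it through.** This is a comparison of text; the protocol gives no figure to reproduce.

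**Step 1: which glucose measurement is it?**

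| Place | What it concerns | Glucose term | Fast |
|---|---|---|---|
| 4.3.5, outcome list | Definition of outcome 3 | Random blood glucose | None implied |
| 4.3.5, procedure | Preparation and assay | Fasting plasma glucose | 24 hours |
| 4.6, procedure | Collection and assay | Fasting blood glucose | Length not given |

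The definition says random; both procedures say fasting. No non-fasting draw is described. The usual-care text in section 4.3.3 mentions monthly visits entered in the electronic record, but does not say that glucose is among the items recorded. The fasting sample is therefore the only described source for outcome 3, and it does not yield the quantity named. The difference between plasma and blood in the two fasting descriptions is loose terminology and is secondary to the conflict between random and fasting.

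**Step 2: the fast.** The 24-hour figure appears once, in section 4.3.5. Section 4.6 is silent on duration, so the two sections do not conflict on this. The reference to national guidelines concerns how samples are collected and analysed; it is not offered as the reason for 24 hours, and the guideline is not identified. What the text does show is an instruction with no reason and no exception, in a population that includes people with diabetes.

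**Step 3: scale.** Section 4.3.6 plans 1,500 participants and allows for 20% loss to follow-up.

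- Baseline samples: 1,500
- Month 10 samples: 1,500 × (1 − 0.20) = 1,200
- Total: 1,500 + 1,200 = 2,700
- Upper bound with no loss: 2 × 1,500 = 3,000

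This counts the samples that fall under the wording. It is not an estimate of bias or of the number of people put at risk.

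**The case against.** The best counter-argument is that no sentence explicitly links the fasting sample to outcome 3. Section 4.3.5 speaks of a blood profile, and routine monthly visits feed an electronic record, so random glucose might come from elsewhere and the fasting sample might serve another purpose. This does not rescue the text. The protocol does not say that glucose is recorded at routine visits, and the only analyte it names for the blood sample is fasting glucose. If outcome 3 did have another source, that source would be undescribed and the outcome still unsettled.

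Several narrower objections do stand:

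- Calling 24 hours wrong needs clinical knowledge or a guideline outside the document. It may be a slip of wording, so it should be put to the clinical investigators for correction or justification.
- The 2,700 samples do not measure the safety issue. Entry requires hypertension, not diabetes, and the protocol does not give the share of participants with diabetes.
- The risk clause in section 5 refers to risks from the interventions, and blood sampling takes place in both arms. Only the part about participant burden bears directly on the fast. Section 5 also sets up an externally led safety committee, though that is general oversight rather than a provision about fasting.
- No difference in sampling between arms is described, so no differential error is shown.

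**Conclusion.** The concern holds: the definition of secondary outcome 3 and its collection procedure are incompatible as written. Which specimen is drawn and how the participant is prepared are protocol matters carried out by clinic staff, so a statistical analysis plan could not resolve this afterwards.

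The scope is limited to one of ten secondary outcomes. No bias figure is claimed, and the primary outcome, margin and sample size are unaffected. If fasting glucose was intended all along, correcting the name loses no data.

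The 24-hour fast is a related but separate point. It would be applied as written to participants with diabetes, without reason or exception, and needs to be corrected or justified. Whether it departs from the national guideline remains open.

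The conclusion assumes that nothing in the protocol text between sections 2 and 4, which was not available for this check, describes a non-fasting sample. Even so, such text would not remove the conflicting wording in sections 4.3.5 and 4.6. This should be put right before samples are collected, but it does not threaten the trial's main conclusion.

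**What to change.** Rename outcome 3 as fasting plasma glucose (mmol/L) and use that one term in sections 4.3.5 and 4.6, at baseline and Month 10, in both arms. If random glucose is what is wanted, keep the name, describe a non-fasting draw and delete the fasting instructions, after checking that no other test in the blood profile needs a fast.

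If fasting is kept, ask the clinical investigators to:

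- correct the 24-hour duration, or justify it against the national guideline, and name that guideline;
- state the same duration in both sections;
- add a safety provision for participants with diabetes, in particular those on glucose-lowering treatment.

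Recording fasting state on the case report form is an optional extra. The cost is wording in two sections and a short clinical check.

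### Protocol 4.3.6: 40 patients per cluster and an ICC of 0.03 require 721 per group, not 614, and 15 × 40 = 600 gives about 83–85% power, not 90%

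*Protocol*

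**What the plan says.** Section 4.3.6 (Sample size and justification) gives every input. The aim is non-inferiority: "Sample size is based on demonstrating the intervention achieves a non-inferior result in systolic blood pressure (SBP"). The margin is fixed ("We will define a non-inferiority margin of 2.5 mmHg") and so is the variability ("the standard deviation of SBP is expected to be about 11 mmHg"). Under individual randomisation, "a sample size of 332 per group would have 90% power with a one-sided type one error of 5"%.

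For clustering, the section sets the cluster size ("We will aim to recruit 40 patients per cluster") and then says: "If we assume a modest intra-class correlation (ICC) of 0.03, indicating a sample size of 614 per group to achieve the same power". From this it concludes that "15 clusters per group of 40 patients each will be required to obtain the minimal required sample size".

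An expected loss to follow-up of 20% raises recruitment to 50 per cluster, 1500 in total. The section closes with two reassurances, neither with a figure. One is "Power will increase if all clusters meet the enrollment target of 50 patients". The other is that averaging each patient's pressure over the last three months should lower the standard deviation and so raise power further.

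**The concern.** The step from 332 to 614 multiplies the sample size by 1.85. A cluster size of 40 with an ICC of 0.03 calls for 2.17. The two numbers cannot both follow from the stated inputs, and a gap of 107 patients per group is too large for rounding. The next sentence then treats 600 as enough to reach 614.

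This paragraph is the protocol's only basis for the size of the trial, and it concerns the primary outcome. If the required number is understated, the non-inferiority test has less power than ethics committees, funders and the monitoring board are told. The risk is a trial that fails to show non-inferiority although the package is no worse than usual care. In a non-inferiority trial such an inconclusive result is easily misread as evidence against the intervention.

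**Working it through.** **Inputs, all from section 4.3.6:** margin 2.5 mmHg; SD 11 mmHg; one-sided α = 5% (z = 1.645); power 90% (z = 1.2816); 40 patients per cluster; ICC 0.03; 15 clusters per group; 20% loss. The section states no expected true difference, so zero is assumed. The next step shows that the protocol assumed the same.

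**1. Individually randomised figure.**
n = 2 × SD² × (z_α + z_β)² / margin² = 2 × 121 × (1.645 + 1.2816)² / 6.25 = 331.6, rounded up to **332**. This matches the protocol exactly, so its method is the normal approximation with a true difference of zero.

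**2. Inflation for clustering.**
Design effect = 1 + (m − 1) × ICC = 1 + 39 × 0.03 = 2.17.
332 × 2.17 = 720.4, rounded up to **721 per group**. The protocol states 614, so the correct figure is 721/614 = 1.17 times as large. At 40 per cluster, 721 is just over 18 clusters per group (721/40 = 18.03).

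**3. What would give 614?**
The implied design effect is 614/332 = 1.849.
- At 40 per cluster, the ICC would be 0.849/39 = 0.0218.
- At ICC 0.03, the cluster size would be 1 + 0.849/0.03 = 29.3.

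The protocol states neither value. Changing the power or the one-sided level while keeping m = 40 and ICC 0.03 does not give 614 either: one-sided 5% gives 521 (80% power) and 606 (85%); one-sided 2.5% gives 660 (80%) and 884 (90%).

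**4. The conclusion against the protocol's own minimum.**
15 × 40 = 600, which is 14 below 614. Since 614/40 = 15.35, even that figure needs 16 clusters per group.

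**5. Power of the planned design.**
SE = 11 × √(2 × 2.17 / 600) = 0.936 mmHg, and 2.5/0.936 = 2.672.
Normal approximation: Φ(2.672 − 1.645) = **84.8%**. Noncentral t with 2 × 15 − 2 = 28 degrees of freedom: **83.2%**.

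**6. The allowance for loss.**
50 × 0.8 = 40, so recruiting 50 only delivers the 40 already assumed. If nobody is lost, the design effect is 1 + 49 × 0.03 = 2.47 and SE = 11 × √(2 × 2.47 / 750) = 0.893. Power is then 87.6% (normal) or 86.1% (t), still below 90%. With 15 clusters per group, 90% power needs about 64 evaluable patients per cluster by the normal approximation, or about 75 with t.

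**7. Sensitivity to the ICC at 15 × 40, SD 11 mmHg.**

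| ICC | Power, normal | Power, t (28 df) |
|---|---|---|
| 0.02 | 90.4% | 89.1% |
| 0.03 (stated) | 84.8% | 83.2% |
| 0.04 | 79.3% | 77.5% |
| 0.05 | 74.1% | 72.3% |

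**The case against.** The arithmetic is not in dispute. The best counter-argument is that 83–85% is not the power of the analysis that will be run. The primary outcome (section 4.3.5) is an average over the last three months, and the mixed model in section 4.6 adjusts for baseline systolic pressure. Both should reduce the residual variance. At 15 × 40 and ICC 0.03, 90% power returns if the effective SD is about 10.0 mmHg (normal) or 9.8 mmHg (t). The equivalent correlation with baseline is about 0.41 or 0.45. At an assumed correlation of 0.5, power would be 92.5% (normal) or 91.4% (t).

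This stands as a caution: the finished trial may well have 90% power. It does not rescue the paragraph. The protocol gives no baseline correlation and no SD for the averaged outcome, and it used neither to derive 614. It presents averaging as a gain on top of 90%, when it would first have to fill a deficit.

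Three smaller objections also have some force. The gap between 600 and 614 is only 2.3%, worth about 0.7 points of power (84.8% against 85.5%). The t-based figures are a reviewer's choice, since the protocol fixes no degrees of freedom. And a misstated power neither biases the estimate nor raises the type I error. All three limit the consequence. None of them makes 614 correct.

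**Conclusion.** The concern holds. On the protocol's own inputs the requirement is 721 per group, not 614, and the planned 600 evaluable per group misses both figures. Power is about 85% by the protocol's own normal approximation, or 83% allowing for the small number of clusters. The chance of missing non-inferiority when the arms are truly equal is therefore about 15–17%, roughly one in six, against the one in ten stated.

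These figures assume SD 11 mmHg, ICC 0.03, equal clusters of 40 evaluable patients, a true difference of zero, and no gain from averaging or baseline adjustment. These are the assumptions the section itself uses, so the comparison is like for like. What is established is that the stated 90% does not follow from the stated inputs. The actual power of the adjusted analysis cannot be worked out from the protocol.

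**What to change.** Correct section 4.3.6 as follows:

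- Replace 614 with 721 per group at 40 per cluster and ICC 0.03.
- Delete the statement that 15 clusters of 40 reach the minimum. State instead that 15 × 40 evaluable patients per group give about 85% power (83% t-based) at ICC 0.03.
- Report power over a range of ICCs, for example about 90%, 85% and 74% at 0.02, 0.03 and 0.05 (normal approximation).
- If a different ICC or cluster size was actually used, state it and justify it from the cited source. The ICC should not be chosen because it restores 90%.
- If the sponsor relies on three-month averaging or baseline adjustment, give the assumed SD or correlation with its source, and show the power with and without it.
- Say that the increase to 50 per cluster only offsets the expected 20% loss, and that full retention would give 87.6% (86.1% t-based).

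The cost is a change of wording and a less favourable stated power. No extra patients or clusters are needed to make the paragraph true. Only a decision to hold 90% power on these inputs would require a larger trial.
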